### Sample size

Previous studies using pre/post EA total sum scores to compare the effectiveness of parent-child interventions [47,48] have reported medium to very large (0.5–1.17) effect size according to Cohen’s [49] criteria. The study is powered to detect a large between-group effect size of Cohen’s d = 0.8 in the primary outcome of change in EA total sum scores between baseline and post-intervention. With a significance criterion of α = 0.05 and power = 80%, the minimum sample size is n = 52 with n = 26 in each sample. Assuming drop-out does not exceed 10%, the aim is to recruit 60 families in total. Furthermore, given the nature of the study involving a short-term home-delivered intervention, n = 30 families in the JP intervention group seems to be a feasible yet significant number.

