### Study procedures

After initial contact and providing a comprehensive explanation of the study, the investigator recruiting participants will confirm that eligibility criteria have been met. Following the provision of written informed consent, eligible dyads will be randomly assigned to only one of the conditions – either the JP dyadic intervention or the psycho-educational parent counseling group, using an allocation ratio of 1:1. A permuted block randomization sequence (block size of 4) will be generated using Microsoft Excel. To ensure balance between the conditions, assignments within each block will be randomized using the = RAND() function. The final sequence will be locked into a static spreadsheet to maintain the integrity of the allocation. Participants will be aware of the condition they will participate in, and the study’s focus on the quality of the mother-child interaction in the assessment meetings. However, they will not be aware of the study design (that the psycho-educational parent counseling group was chosen as the control group).

After the randomization process, the baseline assessment meeting will be conducted at the participants’ homes. The assessment meeting will comprise a mother-child interaction protocol including four consecutive episodes: (a) 10 minutes of free play with a standardized set of toys; (b) 5 minutes of play with a doll and accessories; (c) 7 minutes of social play without toys; and (d) a 3-minute mutual movement activity accompanied by music. All interaction episodes will be video-recorded for subsequent coding. The dyads will then participate in the assigned intervention program. Upon completion of the intervention program, a post-intervention assessment will be conducted using the same mother-child interaction protocol and procedures as the baseline assessment.

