### Mediation measures

Parental Playfulness Scale (PPS) [62] evaluates the parent’s playfulness. The PPS is a standardized observational video analysis tool that assesses parental creativity, imagination, humor, pretend play, and curiosity while playing with their children. The PPS is composed of three subscales: parent’s playfulness, following the child’s lead, and peer-like behavior rated on a 7-point Likert-type scale from 1 to 7, with a higher score signifying more playfulness. All scores are averaged into a single playfulness score for each parent. The PPS will be scored based on the video-recorded episodes of free play and play with a doll. The PPS has been shown to have high interrater reliability of 0.8 [38,63] and has been used to assess the playfulness of parents to children with ID [27].Test of Playfulness (ToP; version 4.2) [64] evaluates the child’s playfulness. The ToP is a standardized observational video analysis tool comprised of 30 items rated on a 4-point Likert-type scale from 0 to 3, evaluating the extent, intensity, and skill of the child at play, with a higher score signifying more playfulness. All scores are averaged into a single playfulness score for each child. The ToP will be scored based on the video-recorded episodes of free play and play with a doll. Studies have established the reliability and validity of the ToP determining goodness-of-fit according to the Rasch analysis model when used with children with ID [35,36], and has been used in previous intervention studies [37].

The outcome measures of EA, child playfulness (ToP), and parent playfulness (PPS) will be coded by blind and trained researchers. Interrater reliability will be determined by comparing 20% of the data to an additional blind and trained scorer using the interclass correlation coefficient [65] to establish consistency of independent ratings.

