## Discussion

The study will discuss the results and clinical applicability of the findings regarding the importance of play and playfulness for the population of children with ID and their mothers. The extensive literature on the importance of play for children’s development and the value of playfulness for the parent-child relationship, supports the hypothesis that enhancing play and playfulness of children with ID and their mothers will contribute positively to the quality of their interactions. Therefore, the JP intervention will focus on enhancing parent-child playfulness, while examining its role as a mechanism of change in parent-child interactions. In order to promote playfulness, the JP intervention will utilize CAT and their unique characteristics to facilitate non-verbal, creative, and reciprocal dyadic play. By shifting the focus from behavior management to fostering playfulness and mutual engagement, JP aims to fill an existing gap in early intervention programs for children with ID and their parents.

The study has several limitations: First, although the sample size is powered to detect the expected effects, a larger sample would be recommended in future research. Second, the relatively short duration of the interventions may limit their impact on the outcome measures. Third, participants are not blinded to their assigned condition. Fourth, the inability to fully control for the influence of external factors, such as additional treatments, may confound the results.

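### The filmed baseline follows randomisation in an open-label trial, with no stated delay in disclosure, so the EA score from which change is measured may already reflect the allocation

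*Protocol article*

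**What the plan says.** Study procedures sets the sequence. Eligibility is confirmed and consent obtained, and then allocation takes place: "Following the provision of written informed consent, eligible dyads will be randomly assigned to only one of the conditions". The visit comes next: "After the randomization process, the baseline assessment meeting will be conducted". The assigned programme follows.

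Before it describes the visit, the same section says: "Participants will be aware of the condition they will participate in, and the study’s focus on the quality of the mother-child interaction". Only the fact that counselling serves as the control is withheld. No section says that allocation is kept from the mother until the baseline has been filmed.

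The primary outcome (Sample size) is "change in EA total sum scores between baseline and post-intervention". EA is scored from filmed social play without toys (Primary outcome measure). The mixed model has time, group and their interaction (Quantitative data), so the baseline score enters as a response.

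Two statements bear on blinding. EA, ToP and PPS "will be coded by blind and trained researchers" (end of Mediation measures). The Discussion lists as a limitation that "participants are not blinded to their assigned condition", but does not mention that baseline comes after allocation.

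**The concern.** A baseline is useful because allocation cannot have influenced it. Here it may have done so. The conditions are openly different: play sessions at home with child and therapist, or online counselling for the mother alone. A mother who knows which she will receive, and knows that the filming concerns how she interacts with her child, may behave differently on camera. EA, IPS, PPS and ToP are all derived from that recorded behaviour.

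Two things are at stake. First, a baseline difference caused by allocation enters the group-by-time contrast directly. Second, a dyad that withdraws between allocation and baseline contributes no outcome at either time. If such losses differ by arm, the mixed model has no data from which to recover them.

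**Working it through.** **1. The plan's own figure.** Inputs from Sample size: d = 0.8 on change in EA, α = 0.05 (taken as two-sided), power 80%, 1:1 allocation. The two-sample t calculation gives 25.5, so 26 per arm and 52 in total, as stated. With 10% drop-out, 52/0.9 = 57.8, so 58, which the planned 60 covers. The sample size is not in question.

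**2. Where a shift enters.** Let b₀ and b₁ be the between-arm shifts in mean EA (JP minus control) caused by knowing the allocation, at baseline and at the post visit. With complete data, the time-by-group term is the difference between arms in mean change:

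- change contrast = true effect + (b₁ − b₀)
- post-only contrast = true effect + b₁

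If the reaction is the same at both visits (b₁ = b₀), the change contrast is unbiased. If it is present only at baseline (b₁ = 0), the change contrast is biased by −b₀ and the post-only contrast is unbiased.

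**3. Illustration.** The documents give no value for b₀ or b₁, so a range is assumed. Let s be the uncancelled shift |b₁ − b₀| in SDs of change. Power is taken from the noncentral t with 26 per arm (50 df), two-sided 5%, and noncentrality d√(26/2) = 3.606d. For the middle column d = s; for the right-hand column d = 0.8 − s.

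| s | Rejection with no true effect | Power at true d = 0.8, shift against JP |
|---|---|---|
| 0 | 5.0% | 80.7% |
| 0.1 | 6.4% | 69.7% |
| 0.2 | 10.9% | 56.4% |
| 0.3 | 18.6% | 42.4% |
| 0.4 | 29.3% | 29.3% |

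**4. Units.** SD of change = SD of score × √(2(1 − ρ)), where ρ is the pre-post correlation (not given). A shift of 0.2 SD of the score is then 0.169, 0.200 or 0.258 SD of change at ρ = 0.3, 0.5 or 0.7.

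**5. Would the planned baseline comparison reveal it?** With 26 per arm the standard error of a baseline mean difference is √(2/26) = 0.277 SD of the score. The 95% margin is 2.009 × 0.277 = 0.56 SD. Shifts of the size illustrated would usually be lost in chance imbalance.

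**The case against.** The strongest reply is that disclosure before baseline is inferred. The text says that mothers will know their condition but not when they learn it, and the SPIRIT schedule, which might settle this, is not shown. That stands. The order of randomisation and baseline is explicit; the time of disclosure is not.

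Second, mothers are still unblinded at the post visit, which repeats the same procedure, so a steady reaction to being filmed would cancel in the change score. That also stands. A reader might infer that any baseline shift biases the result one for one, but this holds only for the part that has gone by the post visit.

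Third, a reader might infer that the VABS-3 covariate is contaminated too. The documents do not support that. Descriptive measures says that the mother completes it but not when, and Study procedures lists only the filmed episodes at the visit. It is exposed only if completed after disclosure.

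Fourth, there are mitigations. Coders are blind, the control label is withheld, both arms receive eight weekly 45-minute sessions, and baseline variables will be compared. These reduce the risk but do not remove it: blind coding cannot undo changed behaviour, the arms remain visibly different, and the baseline comparison is too imprecise to exclude a moderate shift.

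Finally, nothing in the documents indicates that dyads have in fact withdrawn between allocation and baseline. That route is a possibility only.

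**Conclusion.** The concern holds as a weakness in how the procedure is fixed. Baseline is filmed after randomisation in a trial whose participants know their condition, and no safeguard on disclosure is stated. The EA baseline, and with it the change outcome, may therefore depend on allocation. The same applies to the IPS, PPS and ToP baselines.

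The documents do not show that a bias exists, and they do not allow its size or direction to be estimated. The tabulated figures assume a shift that does not cancel between visits. They show how little room a trial sized for d = 0.8 with 26 per arm has, not what has happened. Reading them as an estimate of the trial's error rate would go too far.

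**What to change.** **Dyads not yet enrolled** (60 planned less 40 recruited, so about 20 at the time of the article): complete consent, eligibility, the VABS-3 and the filmed baseline before allocation is drawn, or at least before it is disclosed. State this sequence in Study procedures.

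**Dyads already assessed:** report when each learned its allocation, and the number lost between allocation and baseline by arm. Add a supportive comparison of post-intervention EA that does not use the baseline. Note that it keeps any reactivity persisting to the post visit (b₁ above), so it complements the change analysis and is not a clean replacement. It is also less precise than the change score if ρ exceeds 0.5. Add the ordering to the limitations in the Discussion.

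**Cost:** a short procedural amendment, with no extra visit or staff, and one additional analysis. The drawback is two baseline procedures within one trial, with most dyads under the old order.

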## Methods

### Study design

This mixed-methods RCT aims to compare between two conditions: JP dyadic intervention and psycho-educational parent counseling. The quantitative data assessing participants’ outcomes from both conditions will be collected at two-time points: before participation in either program and one week upon program completion. The qualitative data will be based on interviews with 12 mothers participating in the JP intervention condition and will be collected at two-time points: one week after participation in the JP intervention and a follow-up two months later. The qualitative component will examine mothers’ subjective experiences and meaning-making processes, with particular attention to how they interpret their engagement in the JP dyadic intervention. Incorporating a qualitative arm responds to recent calls for mixed-methods approaches that foreground participants’ lived experiences and perspectives, thereby enriching the evaluation of the intervention processes and outcomes [45]. This approach is especially pertinent for dyadic interventions, where relational dynamics and experiential change may not be fully captured by quantitative measures alone. The qualitative strand in this research is intended to provide in-depth understanding of the intervention experience and potential mechanisms underlying its effects, rather than reproducing between-group comparisons.

Fig 1 depicts SPIRIT schedule of enrollment, interventions, and assessments and Fig 2 depicts the study’s CONSORT flow diagram [46].

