In addition, qualitative interviews with a subset of mothers in the JP group will be conducted at post-intervention and two-month follow-up. As the study aims to provide in-depth understanding of the intervention experience and potential mechanisms underlying its effects on the mother-child interactions, the Interpretative Phenomenological Analysis (IPA) methodology was chosen to allow idiographic and phenomenologically grounded exploration of the mothers’ experiences. IPA guidelines recommend small, relatively homogeneous samples to permit detailed case-by-case analysis prior to cross-case interpretation [50]. Therefore, interviewing a subsample of 12 mothers from the intervention group will allow for sufficient experiential depth while maintaining analytic rigor consistent with IPA methodology. The mothers will be selected in a purposeful sampling process [50]. All eligible mothers who complete the JP intervention will be invited to take part in a qualitative part of the study immediately following completion of the intervention, and recruitment will continue until the target sample of 12 participants is reached. The interviews will be conducted in the mothers’ homes by a member of the research team who was not involved in intervention delivery. The post-intervention interview will be semi-structured and in-depth. The two-month follow-up interview will incorporate an Interpersonal Process Recall procedure, during which the mother and interviewer will jointly watch selected video excerpts from the intervention sessions and reflect on them [51,52]. All interviews will be audio-recorded and transcribed verbatim for qualitative analysis.

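### JP mothers alone are invited to the qualitative part before the filmed primary assessment, and the order of the first interview and the filming is not fixed

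*Protocol article*

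**What the plan says.** All of this is in the protocol article.

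- **Filming (Study design).** Quantitative outcomes in both arms are collected "before participation in either program and one week upon program completion".
- **Interviews (Study design).** The qualitative data come from "interviews with 12 mothers participating in the JP intervention condition". They are collected "one week after participation in the JP intervention and a follow-up two months later".
- **Invitation (Study procedures).** Eligible mothers who complete JP "will be invited to take part in a qualitative part of the study immediately following completion of the intervention". The stopping rule for these invitations is that "recruitment will continue until the target sample of 12 participants is reached". Interviews are done at home "by a member of the research team who was not involved in intervention delivery".
- **What mothers know (Study procedures).** "Participants will be aware of the condition they will participate in, and the study’s focus on the quality of the mother-child interaction". On the other hand, "they will not be aware of the study design (that the psycho-educational parent counseling group was chosen as the control group").
- **What is scored (Primary outcome measure; Mediation measures).** The EA scales are coded from a 7-minute filmed play episode. Four of their six dimensions rate the mother. The Parental Playfulness Scale (PPS) is coded from other episodes of the same filmed assessment. The EA and playfulness coders are blind.
- **Limitations (Discussion).** The article acknowledges that mothers know their condition. It does not mention the interviews in this connection.

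**The concern.** The primary outcome is the mother's and child's behaviour on camera. Anything that reaches mothers in one arm only, between the end of the programme and the filming, can alter that behaviour without being part of the therapy.

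The qualitative part is not remote from what is scored. According to the Research questions, it asks how JP shapes the mother's relationship with her child and which practices encourage playful interaction. A mother who has just discussed these topics in depth, or who knows she is about to, may play more attentively or more playfully when filmed. Any such shift would be counted as a treatment effect on EA and on the PPS. Blind coding guards against a coder's expectations. It does not guard against a real difference in recorded behaviour.

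There is a lesser concern about concealment. Mothers are not told that counselling serves as the control. A request made only to JP mothers, about JP, could suggest to them that JP is the programme of interest.

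**Working it through.** **1. The plan's own figure.** Sample size: d = 0.8, alpha 0.05 (two-sided assumed, since sidedness is not stated), power 80%. The normal approximation gives 25 per arm. The two-sample t-test gives 25.5, rounded up to 26 per arm, or 52 in total, with power 80.7%. Allowing for 10% dropout, 52 / 0.9 = 57.8, rounded up to 58, which is within the 60 planned. The stated size is reproduced and is not in dispute.

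**2. The sequence of contacts.**

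| Contact | JP arm | Counselling arm | Stated time |
|---|---|---|---|
| Invitation to qualitative part | yes, until 12 are recruited | no | immediately after completion |
| Filmed post-assessment | yes | yes | one week after completion |
| First interview | 12 mothers | none | one week after completion |
| Second interview with video review | the same subset | none | two months later |

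Read literally, the invitation precedes the filming. The first interview and the filming share one nominal time point and no order is given. The second interview comes after the primary outcome and is not at issue.

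**3. How many mothers.** Interviewed: 12 / 30 = 40% of the JP arm as randomised. All 12 are completers, so the share is 12 / 26 = 46% if only the minimum 26 are evaluable. Invited: at least 12. The number reaches 30 only if most mothers decline, because inviting stops at 12 recruits.

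**4. Possible size (illustration only).** The article gives no figure for the effect of an interview on filmed behaviour. Assume that all 12 interviews precede filming, that each interviewed mother's score shifts by b SD, and that the others do not shift. Then

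shift in JP mean = (share interviewed) × b.

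The rejection rates below are two-sided, with no true effect, 26 per arm and nominal 5%, from the noncentral t distribution.

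| Assumed b | Share 12/30: shift | Rejection | Share 12/26: shift | Rejection |
|---|---|---|---|---|
| 0.1 | 0.04 SD | 5.2% | 0.05 SD | 5.3% |
| 0.2 | 0.08 SD | 5.9% | 0.09 SD | 6.2% |
| 0.3 | 0.12 SD | 7.1% | 0.14 SD | 7.8% |
| 0.5 | 0.20 SD | 10.9% | 0.23 SD | 12.9% |

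Relative to the design effect, for b of 0.2 and 0.5 with 12 of 30: 0.08 / 0.8 = 10% and 0.20 / 0.8 = 25%. If filming always precedes the interview, the interview contributes nothing to these shifts.

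**5. Who can still be reached.** Status and timeline reports 40 dyads recruited and 30 completed. Of the 60 planned, 60 − 30 = 30 had still to complete. If completers are split evenly between arms, about 15 are JP, so all 12 interviews could already have been held.

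**The case against.** The strongest reply is that the order of two contacts in the same week is operational detail, which a journal article may leave to the full protocol. Study procedures describes the post-intervention filming first and then introduces the interviews, so filming followed by interview is a natural reading. This has force for the interview. It does not answer the invitation, whose time is stated and, read literally, falls before the filming.

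A second reply is that the mechanism is thin. JP mothers have already had eight weekly sessions in which a therapist models playfulness, both arms know that interaction quality is being assessed, and the most intensive reflection, the joint video review, comes two months later. All of this is true and makes a large effect less likely. It does not make the arms alike in the week before filming.

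A third reply concerns two stronger conclusions that a reader might draw. One is that concealment of the control arm cannot hold. The text does not support this: an invitation to talk about JP does not reveal what the counselling arm is for, and nothing says that counselling mothers hear of the interviews. The concealment claimed is narrow, and the Discussion already concedes that mothers know their own condition. The other is that the JP arm as a whole is primed. That depends on an order the article does not state and on an effect it does not quantify, and for the interview it would concern at most 12 mothers. On both conclusions the reply stands.

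**Conclusion.** The point holds as a correctable weakness in timing. It is not a demonstrated bias. The article fixes a JP-only invitation before the primary assessment and leaves a JP-only interview free to precede it. Either could influence the mother's filmed behaviour in one arm, and blind coding would not remove that influence. The concealment of control status may be weakened but is not defeated.

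The size is unknown. The 0.08 to 0.20 SD range rests on two assumptions that the article neither supports nor excludes: that all 12 interviews come before filming, and that each shifts the mother's score by 0.2 to 0.5 SD. If filming comes first, the interview adds no bias, and only the early invitation remains.

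**What to change.** - **Study design and Study procedures:** state that each mother is invited to the qualitative part, and interviewed, only after her filmed post-assessment is complete. The same home visit is acceptable.
- **Dyads already completed:** record and report whether the invitation and the interview came before or after the filming.
- **Analysis:** keep all randomised dyads in the primary analysis. Any comparison by contact order should be descriptive only. Dropping JP dyads interviewed before filming would be a post-randomisation exclusion in one arm, of mothers who completed and agreed to be interviewed. It could leave as few as 30 − 12 = 18 JP dyads and introduce selection bias of its own.
- **Statement on what mothers know:** add that the JP-only invitation may have weakened concealment for mothers invited before filming.

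The cost is a slightly later invitation and a few sentences of protocol text. The sample size does not change. The reach is limited if most of the 12 interviews have already been held; in that case the reporting of order is the main benefit.
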